### Objectives {7}

This randomized controlled trial (RCT) aims to determine the efficacy of REACH (REsilient Active CHildren; https//reachkids.info), a web-based preventive social learning and cognitive behavior therapy (SLCBT) intervention delivered to parents with IBS, compared to an educational web-based safety comparison condition (EC) (aim 1). This trial also aims to determine the contribution of changes in parental risk and protective factors in mediating treatment effects (aim 2). Finally, we aim to determine cost savings of implementing this preventive intervention on health care expenditures and resource utilization over 18 months (aim 3).

The following hypotheses will be tested: (1) Parents receiving SLCBT will show lower solicitous behaviors (primary outcome) and lower levels of risk factors, including anxiety, parenting stress, and catastrophizing, than those receiving EC; (2) Parents receiving SLCBT will show increased levels of protective factors, including higher positive affect and social support, than those receiving EC; (3) Children of parents trained in SLCBT will have better physical, psychological, social, and school functioning, and fewer abdominal symptoms than those of parents in EC; (4) Changes in parental risk and protective factors will mediate treatment effects on child health-related quality of life; and (5) The SLCBT group will demonstrate superiority in a cost savings analysis compared to the EC group.

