##### Social learning and cognitive behavioral therapy (SLCBT) condition

Participants assigned to the SLCBT group will complete a 4-week web-based intervention. The website includes an introductory module, three skills-training modules (i.e., strategies to promote wellness behaviors, use adaptive cognitive coping, model wellness behaviors for their children, and determine when it is appropriate to take further action regarding potential illness in their child), and a brief maintenance and summary module. The web modules were designed to be visually attractive and interactive in order to engage participants through using brief questions to assess participant knowledge, interactive question/answer components, instructional videos, and storyboards that participants can click through. Screenshots can be seen in Fig. 3. Additionally, participants are provided a “Toolbox” in which informational handouts can be accessed, downloaded, and printed. The handouts provide a summary of the knowledge provided in each module. Participants in each group are instructed to log in to the website for 3–4 weeks, approximately 20–30 min per week. Research team members will regularly assess web program usage for all participants and will send reminders up to two times each week as needed to encourage regular usage and completion of all modules.

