Aim 3: Determine cost savings of implementing this preventive intervention on health care expenditures and resource utilization over 18 months. To assess hypothesis 5 (that the SLCBT group will demonstrate cost savings in relation to the EC group), we will first estimate total health care costs in each group, which will be the sum of direct medical costs, direct non-medical costs, and indirect costs. Direct medical costs for each group will be estimated by multiplying utilization estimates for each reported service by the service-specific unit cost from the most recent Medical Expenditure Panel Survey (MEPS) [67], and then summing the costs of all services used. Direct non-medical costs for each arm will be the sum of parent-reported out-of-pocket expenses for special foods, equipment, and transportation to medical appointments. Indirect costs for each arm will be estimated by multiplying parent-reported hours of missed work and leisure time due to caring for their child (i.e., when absent from school due to illness behavior, taking to medical appointments) by the current mean hourly wage for a US worker from the Consumer Price Index of the US Bureau of Labor Statistics [68]. Cost superiority will be indicated by the arm with lower total health care costs if arms are equal in size, or by the average health care cost per family if they are not. Should the SLCBT arm prove superior as hypothesized, intervention-related cost savings per family will be estimated as the difference in average health care costs per family (health care cost/familySLCBT − health care cost/familyEC).

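### Aim 3's planned saving is a difference in health care costs that excludes programme cost; it should be labelled so, with a net figure added before claiming that implementing REACH saves money

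*Protocol article*

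**What the plan says.** Aim 3 reads: "Determine cost savings of implementing this preventive intervention on health care expenditures and resource utilization over 18 months". The Objectives {7} use the same framing. Hypothesis 5 is narrower and compares the SLCBT group with the EC group.

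The cost total for each arm is defined as "total health care costs in each group, which will be the sum of direct medical costs, direct non-medical costs, and indirect costs", and each part is then itemised:

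- Direct medical: reported service use priced at unit costs from a national expenditure survey.
- Direct non-medical: "parent-reported out-of-pocket expenses for special foods, equipment, and transportation to medical appointments".
- Indirect: "parent-reported hours of missed work and leisure time due to caring for their child", priced at the mean US hourly wage.

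The cheaper arm is called superior, on totals if the arms are equal in size and on the per-family average if not. If that arm is SLCBT, "intervention-related cost savings per family will be estimated as the difference in average health care costs per family".

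On delivery, Intervention description {11a} asks parents in both groups for 3–4 weeks of use at about 20–30 minutes a week. Staff follow usage for everyone and "will send reminders up to two times each week as needed to encourage regular usage and completion of all modules". Strategies to improve adherence {11c} adds that the website itself tracks progress and emails reminders, with further staff reminders only where needed.

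**The concern.** The framing speaks of implementation and of savings related to the intervention, while the formula has no term for what the intervention costs to run. Hosting and upkeep, staff reminder time and the hours parents spend on the modules appear nowhere in the list. The cost instrument in Table 2 (the CSRI) collects only child health care costs, so it would not supply them either. This is not detail deferred to a fuller document: the components and the formula are both fixed here.

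At stake is what may be concluded. The superiority rule has no margin, so any positive difference in care costs, however small, leads to a reported saving per family. The article presents REACH as scalable for wide dissemination. A health system reading the result would ask whether adopting REACH saves money compared with not adopting it, and the planned figure answers a different question.

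**Working it through.** The article states no cost, saving or delivery-cost figure, so there is nothing to reproduce. The check is of the definition, followed by the algebra of what the figure estimates.

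**1. Delivery terms in the cost definition.** Of the three itemised components, 0 include programme delivery. The indirect component counts parent hours, but only those lost to caring for the child, not those spent on the modules.

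**2. What the planned figure estimates.** Let H_R, H_E and H_0 be mean health care cost per family, as the plan defines it, under REACH, under EC and with no programme. Let c_R and c_E be the delivery costs per family. Write G = H_E − H_R, so that a saving is positive (the plan prints the subtraction the other way round).

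- Planned contrast: G.
- REACH versus EC with delivery charged to both arms: G − (c_R − c_E). If c_R and c_E are close, this is close to G.
- REACH versus no programme: (H_0 − H_R) − c_R = G + (H_0 − H_E) − c_R. If EC does not change health care costs, H_0 = H_E and this becomes G − c_R.

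Under that assumption the planned figure exceeds the net saving by exactly c_R.

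**3. What the documents give on c_R.**

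- Parent time: 3 × 20 min = 60 min = 1 h, up to 4 × 30 min = 120 min = 2 h per family.
- Staff reminders: at most 2 per week × 4 weeks = 8 per family over the 4-week programme. This is a ceiling, because they are sent as needed and the website sends its own.
- Hosting, maintenance, staff minutes and wages: not given.

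**4. Range under assumed prices (none from the documents).**

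- Parent time at an assumed $20–40 per hour: 1 × 20 = $20 to 2 × 40 = $80.
- Reminders at the ceiling of 8, with an assumed 5–10 staff minutes each, take 40–80 min. At an assumed $25–40 per hour that is 40/60 × 25 = $16.7 to 80/60 × 40 = $53.3. For a family that keeps to schedule it could be near $0.

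**5. Effect on the conclusion (assumed G and c_R).**

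| G | c_R | Net = G − c_R |
|---|---|---|
| $200 | $25 | $175 |
| $200 | $50 | $150 |
| $200 | $100 | $100 |
| $200 | $200 | $0 |
| $100 | $200 | −$100 |

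The sign changes only when c_R exceeds G. The documents do not say whether that is likely.

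**The case against.** The strongest reply is that the plan computes what it names. The aim is bounded by its reference to health care expenditures and resource use, hypothesis 5 is relative to EC, and each computed quantity is called a health care cost. No net-return or budget-impact figure is promised. This largely stands for the randomised contrast. What it leaves open is the wording about implementing the programme and about intervention-related savings, which invites a conclusion the quantity cannot carry.

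A second reply is that delivery costs cancel. EC is designed to match SLCBT in time and attention, the instructed weekly minutes apply to both groups, monitoring covers all participants, and Who will be blinded {17a} says that both arms share one website platform. This stands too. A reader might infer that the SLCBT-versus-EC figure is itself biased, or that the superiority call is an error. The documents do not support either. The gap arises only when the figure is read as REACH against no programme, an arm this trial does not have.

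A third reply is that subtracting only REACH's delivery cost mixes comparators, since the health care costs still come from families who received EC. That is correct, and it is why the net figure needs its assumption stated.

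Finally, parents' self-paced module time is arguably not the same kind of cost as hours lost to a sick child. That is a fair point of perspective, best met by showing the net figure with and without it.

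**Conclusion.** The point holds as one about labelling and about the conclusion that Aim 3 can support. The planned contrast is a sound difference in health care costs between arms, gross of programme cost. As a statement about rolling REACH out against no programme, it is too favourable by the delivery cost per family, provided EC does not itself change health care costs.

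The size of that cost is unknown. The documents fix only 1 to 2 parent hours and a ceiling of about 8 staff reminders; every dollar figure above is an assumption. A reader might infer that delivery cost would cancel or reverse the saving. Nothing in the documents shows this, and web delivery may be cheap per family. Equally, nothing shows that the cost is zero.

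This concerns a secondary aim. The primary outcome, the randomised comparison and the conduct of the trial are unaffected.

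**What to change.** 1. Keep the SLCBT-versus-EC contrast as planned and label it *difference in health care costs, excluding programme cost*.
2. Add a secondary net saving per family = (mean EC cost − mean SLCBT cost) − REACH delivery cost per family. Delivery cost covers hosting and maintenance, the staff reminder time that a rollout would need (leaving out monitoring done only for the trial), and parent programme time at the wage already used for indirect costs. Show the result with and without parent time.
3. State next to it the assumption that EC does not change health care costs.
4. Base any statement that implementing REACH saves money on the net figure.

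The cost is a small log of staff time and hosting expense and one more line in the cost table. Module completion is already recorded by the website. Recruitment is estimated to run to April 2027, which leaves room to log these resources. The reported saving will look less favourable.

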**Methods:**

Parents with IBS who have children ages 4–7 years are recruited via community-based approaches (e.g., social media advertisements, school electronic distribution, research networks) and health care providers. The target sample is 460 parents randomized to REACH, a web-based social learning and cognitive behavior therapy (SLCBT) intervention or an educational web-based safety comparison condition (EC). Participants will be assessed at baseline, 6-week (immediate post-intervention), 6-month, 12-month, and 18-month follow-up periods (months post-completion of intervention). The primary outcome is change in parental solicitous/protective behaviors. Secondary outcomes include parent risk and protective factors, child health and symptom outcomes, and health care utilization and cost savings.

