### Trial design {8}

This study utilizes a RCT with parallel 1:1 assignment to two study arms, (1) REACH, a SLCBT prevention intervention, and (2) an educational comparison condition (EC). Figure 2 provides the study recruitment flow and condition allocation.

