## Statistical methods

### Statistical methods for primary and secondary outcomes {20a}

#### General analytic procedures

All main analyses will be intention-to-treat analyses, including all participants randomized regardless of intervention compliance. Missing values due to dropouts will be imputed with well-established methods that reduce bias in estimates such as multiple imputation, full information maximum likelihood, and empirical Bayes estimation, or multiple imputations with chained equations (MICE), if a substantial amount of missing data exists.

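### Aim 3 declares cost superiority from point estimates alone, so with no true cost difference the intervention arm is declared superior half the time

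*Protocol article*

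**What the plan says.** The Objectives section {7} lists hypothesis 5 among those to be tested: "The SLCBT group will demonstrate superiority in a cost savings analysis compared to the EC group". Under Statistical methods {20a}, Analyses by aims, Aim 3 adds medical, non-medical and indirect costs for each arm and then gives the rule: "Cost superiority will be indicated by the arm with lower total health care costs if arms are equal in size". When the two arms differ in number, the comparison switches to the mean per family. If SLCBT comes out lower, "intervention-related cost savings per family will be estimated as the difference in average health care costs per family".

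No confidence interval, test, significance level or margin is attached to the rule or to the saving. Section {20b} says that all analyses are described in {20a}. The sample size section {14} covers only the primary outcome and mediation.

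Two general statements in {20a} also bear on this point: "All main analyses will be intention-to-treat analyses, including all participants randomized regardless of intervention compliance", and "Missing values due to dropouts will be imputed with well-established methods that reduce bias in estimates".

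**The concern.** Two sample means or totals are almost never identical, so this rule always names a winner. It cannot return the answer that the data do not distinguish the arms. Yet the result is called superiority and is presented as the test of a directional hypothesis.

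The saving is estimated only when SLCBT wins, so any saving reported will favour SLCBT, even when it is noise. Nothing reported beside it would show a reader how uncertain it is. Child health care costs may well be skewed, in which case a few expensive families can decide the winner.

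At stake is the conclusion of one of the trial's three aims, and a monetary saving per family that others may quote.

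**Working it through.** The article states no error rate, power or sample size for Aim 3, so there is no figure of the plan's own to reproduce. The error rate of the rule can be computed directly.

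**Inputs from the article.** Target sample: "The target sample is 460 parents randomized to REACH" or the comparison condition. Allocation: "This study utilizes a RCT with parallel 1:1 assignment to two study arms". Exact balance therefore gives 460/2 = 230 per arm.

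**Assumptions.** The article gives no coefficient of variation (CV) for cost and no dropout rate. I take CV = 1, 2 and 3, the same in both arms. Where dropout enters, the rates are illustrative.

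**1. No true difference, equal arms.** With identical cost distributions and equal numbers, either arm is equally likely to be lower, so P(SLCBT declared superior) = 0.50. This needs no assumption about skewness or CV. Simulation (20,000 trials per scenario, log-normal costs, 230 per arm) gives 0.496 to 0.503.

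**2. SLCBT truly dearer.** Let x be the excess as a fraction of mean cost in the comparison arm (EC). With a normal approximation for the difference in means,

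SE = CV × √[(1 + (1 + x)²)/230], and P(SLCBT declared superior) = Φ(−x/SE).

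For x = 0.10: √(2.21/230) = 0.0980, so P = Φ(−1.02/CV).

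| CV (assumed) | x = 0.05 | x = 0.10 |
|---|---|---|
| 1 | 0.30 | 0.15 |
| 2 | 0.40 | 0.31 |
| 3 | 0.43 | 0.37 |

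**3. Size of the saving reported from noise.** With no true difference, the expected saving given that SLCBT wins is about 0.80 × CV × √(2/230) = 0.80 × CV × 0.0933. That is about 7% of mean cost at CV 1 and 22% at CV 3.

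**4. Meaning of equal arms.** Suppose 25% of SLCBT and 15% of EC families have no cost data, unrelated to their costs, leaving 172 and 196 reporters.

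- Per-family average: P stays at 0.50 (simulated 0.500 to 0.505).
- Totals summed over reporters without imputation: P = Φ[(196 − 172)/(CV × √368)] = Φ(1.25/CV), or 0.90, 0.73 and 0.66 for CV 1, 2 and 3 (simulated 0.89, 0.74, 0.69). At 20% versus 15% the values are 0.73, 0.62 and 0.58.

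**5. With an interval.** If superiority requires the 95% confidence interval for the difference in mean cost to exclude zero in favour of SLCBT, the nominal false-confirmation rate is 2.5%. Simulation at 230 per arm gives 2.6%, 2.2% and 1.8% for CV 1, 2 and 3.

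**The case against.** The strongest general defence is that an article condenses the plan, and that the method for a secondary cost comparison belongs in the statistical analysis plan. That would hold if the article were silent. It instead states what will count as superiority, and {20b} points to {20a} as the place where all analyses are described. An analysis plan that required an interval would be changing the stated rule. By contrast, Aim 1 in the same section is given a multilevel model with tests.

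A reader might also infer that higher dropout in the REACH arm will make it look cheaper, and take the 66% to 90% figures in step 4 as the rule's error rate. The article does not support that. When arms are unequal the rule moves to the per-family average, which stays at 50% if dropout is unrelated to cost. The general procedures also commit main analyses to all randomized participants and provide for imputation. The inflation needs two unstated things together: that equal size means randomized size, and that totals are summed over reporting families without imputation. What stands is an ambiguity that the text does not resolve. When the analysed arms really are equal, totals and means rank them identically, so the total rule adds nothing.

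Three other possible criticisms are not errors. Defining the saving as SLCBT minus EC is a printed sign convention. Omitting the cost of delivering REACH reflects a different question from the stated one about health care expenditure. Not naming baseline cost as a covariate is a missed gain in precision at most.

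**Conclusion.** The rule is wrong as written: it treats a difference between two point estimates as superiority. The 50% false-confirmation rate under no difference rests only on identical distributions and equal arms. The 15% to 37% rate when SLCBT is 10% dearer rests on 230 families per arm, a normal approximation and an assumed CV of 1 to 3; a different spread of costs would move it. No inflation from dropout is asserted beyond the one reading described above.

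This should be fixed, because as it stands Aim 3 cannot support a superiority claim. The aim is secondary, and the primary outcome, parental protectiveness on the ARCS, is unaffected.

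**What to change.** Replace the rule in Aim 3 with one comparison that applies whether or not the arms are equal in size:

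- Compare mean 18-month cost per randomized family by a method suited to skewed costs, such as a bootstrap of the difference in means or a gamma model with log link.
- Impute missing waves of the service-use inventory (CSRI), as the general procedures already allow.
- Report the difference with a 95% confidence interval whichever arm is lower, and claim superiority only if the interval excludes zero in favour of SLCBT.
- Delete the total-cost criterion, which also removes the question of what equal size means.
- Optionally, adjust for the CSRI cost already collected at T1.

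The change is to wording, with slightly more analysis and no new participant data. The price is that the claim becomes harder to win. With 230 per arm, the saving detectable with 80% power at two-sided 5% is (1.96 + 0.84) × CV × √(2/230), about 26%, 52% and 78% of mean cost at CV 1, 2 and 3, before any gain from baseline adjustment. The interval may therefore be wide, and reporting it would show how little or how much the trial can say about cost.

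### Aim 3 plans the per-family cost difference only if SLCBT is observed to be cheaper, so its one prespecified cost contrast is favourable by construction

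*Protocol article*

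**What the plan says.** The Objectives section of the protocol article gives the third aim as follows: "we aim to determine cost savings of implementing this preventive intervention on health care expenditures and resource utilization over 18 months". The matching hypothesis 5 is directional: "The SLCBT group will demonstrate superiority in a cost savings analysis compared to the EC group".

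The Aim 3 paragraph under Analyses by aims (section 20a) sets out three steps.

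1. Costs by arm, without any condition: "we will first estimate total health care costs in each group, which will be the sum of direct medical costs", plus direct non-medical and indirect costs.
2. A rule for naming the cheaper arm: "Cost superiority will be indicated by the arm with lower total health care costs if arms are equal in size", or by average cost per family if the arms differ in size. Either arm can be named. The rule contains no test, interval or margin.
3. The between-arm contrast, with a condition attached: "Should the SLCBT arm prove superior as hypothesized, intervention-related cost savings per family will be estimated as the difference" in average costs per family, SLCBT minus EC.

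The article describes no other between-arm cost contrast, and section 20b refers back to section 20a for all analyses.

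**The concern.** Step 3 lets the observed result decide whether the effect estimate is produced. Determining the saving from an intervention requires the difference whichever way it falls. If the difference is estimated only when it is favourable, it comes from a truncated distribution. Its expectation is then a saving even when the true difference is zero or SLCBT costs more.

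Because superiority means only a lower observed cost, chance alone meets the condition half the time when there is no effect. At stake is the headline cost figure of a named aim: when it appears it leans towards SLCBT, and if EC is cheaper the plan offers no contrast to put in its place.

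This is not a detail left to the statistical analysis plan. The article states the condition explicitly, so an analysis plan that follows it takes over the selection.

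**Working it through.** The article states no cost SD, cost effect size or cost power, so there is no figure of its own to reproduce. The calculation below shows what the rule does.

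**Inputs from the article.** Target sample of 460 (Abstract, Methods: "The target sample is 460 parents randomized to REACH") and 1:1 allocation (Trial design: "This study utilizes a RCT with parallel 1:1 assignment to two study arms"). The contrast D is mean cost per family, SLCBT minus EC, so a saving is negative.

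**Assumptions.** D is approximately normal with mean θ, the true difference in cost-SD units. The true difference ranges from +0.10 to −0.30 SD. N = 368, which is 80% of 460, serves as a sensitivity value.

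**The condition in terms of D.** With equal arms, the order of the totals is the order of the averages. With unequal arms, the averages are compared directly. Either way, SLCBT is superior exactly when D < 0.

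**Formulas.**
- Standard error with 1:1 allocation: se = √(4/N). This gives 0.0933 SD for N = 460 and 0.1043 SD for N = 368.
- Probability that a saving is estimated: P(D < 0) = Φ(−θ/se).
- Mean of the estimate when it is produced: E[D | D < 0] = θ − se·φ(θ/se)/Φ(−θ/se).

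**Worked cases, N = 460.**
- θ = 0: the probability is 0.50 and the mean is −0.0933 × 0.3989/0.5 = −0.074 SD.
- θ = −0.10: θ/se = −1.072, φ = 0.2245 and Φ(1.072) = 0.858. The mean is −0.10 − 0.0933 × 0.2245/0.858 = −0.124 SD, an overstatement of 0.0244/0.10 = 24%.

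**Results.**

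| True difference (SD) | N = 460: probability | N = 460: mean estimate | N = 368: probability | N = 368: mean estimate |
|---|---|---|---|---|
| +0.10 (SLCBT dearer) | 0.142 | −0.048 | 0.169 | −0.056 |
| 0 | 0.500 | −0.074 | 0.500 | −0.083 |
| −0.10 | 0.858 | −0.124 | 0.831 | −0.132 |
| −0.20 | 0.984 | −0.204 | 0.972 | −0.207 |
| −0.30 | 0.999 | −0.300 | 0.998 | −0.301 |

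At a true saving of 0.20 SD the overstatement is 0.0038/0.20 = 1.9% with N = 460 and 0.0068/0.20 = 3.4% with N = 368. At 0.30 SD it is below 0.3% in both.

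**Without the condition.** E[D] = θ in every row, so there is no selection bias.

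To express an SD figure as a share of mean cost, multiply by the coefficient of variation of cost, which the article does not give. For assumed values of 1, 2 and 3, the 0.0744 SD at θ = 0 and N = 460 becomes 7%, 15% and 22% of mean cost.

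**The case against.** The strongest reply is that the conditional step is a single subtraction of two quantities that are planned in every case. Both arm costs are estimated first, and EC can be named the cheaper arm. Truncation misleads only a reader who sees the selected number alone. The sentence may also have been meant merely to say when the difference may be called a saving. The matter concerns the third aim, not the primary outcome.

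Much of this stands. A reader might infer that a cost increase under REACH would never be estimated, or that unfavourable cost figures would be kept from view. The document does not support that. The arm costs are unconditional, an increase follows from them by subtraction, and nothing says they would be withheld. The article also commits to publication, registry reporting and release of de-identified data.

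Two things remain. A subtraction made by the reader is not a prespecified analysis, and the sentence as written attaches the condition to estimating the difference, not to naming it. If only the label was meant, the wording should say so.

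**Conclusion.** The point holds in limited form. Costs in both arms and the identity of the cheaper arm are planned either way, but the per-family difference is planned only when SLCBT has the lower observed cost. The one prespecified cost contrast is therefore favourable by construction, and none is planned if EC is cheaper.

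The effect matters when the true difference is near zero and becomes negligible at a true saving of 0.2 to 0.3 SD. The article gives no expected cost effect that would show which range applies. The sizes rest on a normal approximation for the mean difference and on the SD scale. That the estimate can take only one sign follows from the text alone and needs no assumption.

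This is a worthwhile correction to a named aim. It is no threat to the primary analysis.

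**What to change.** In the last sentence of the Aim 3 paragraph in section 20a, delete the opening clause that makes the estimate depend on SLCBT being superior. State instead that the difference in mean 18-month cost per family will be estimated and reported with its interval whatever its sign, and that hypothesis 5 will be judged from that estimate. The interval method can be left to the statistical analysis plan.

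The same edit can settle the direction of subtraction: SLCBT minus EC gives a negative number for what the sentence calls a saving. Reversing the sign alone would leave the selection in place.

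The cost is one sentence. No new data are needed, and the calculation is the same one run in all cases. Recruitment is estimated to finish by April 2027 with 18-month follow-up after that, so the change can be made before the cost data are complete.
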